## Abstract

**Background:**

Adequate monitoring tools are required to optimise the immunosuppressive therapy of an individual patient. Particularly, in calcineurin inhibitors, as critical dose drugs with a narrow therapeutic range, the optimal monitoring strategies are discussed in terms of safety and efficacy. Nevertheless, no pharmacokinetic monitoring markers reflect the biological activity of the drug. A new quantitative analysis of gene expression was employed to directly measure the functional effects of calcineurin inhibition: the transcriptional activities of the nuclear factor of activated T-cell (NFAT)-regulated genes in the peripheral blood.

**Methods/Design:**

The CIS study is a randomised prospective controlled trial, comparing a ciclosporin A (CsA)-based immunosuppressive regimen monitored by CsA trough levels to a CsA-based immunosuppressive regimen monitored by residual NFAT-regulated gene expression. Pulse wave velocity as an accepted surrogate marker of the cardiovascular risk is assessed in both study groups. Our hypothesis is that an individualised CsA therapy monitored by residual NFAT-regulated gene expression results in a significantly lower cardiovascular risk compared to CsA therapy monitored by CsA trough levels.

**Discussion:**

There is a lack of evidence in individualising standard immunosuppression in renal allograft recipients. The CIS study will consider the feasibility of individualised ciclosporin A immunosuppression by pharmacodynamic monitoring and evaluate the opportunity to reduce cardiovascular risk while maintaining sufficient immunosuppression.

**Trial registration:**

EudraCT identifier 2011-003547-21, registration date 18 July 2011

https://www.clinicaltrialsregister.eu

## Background

### Current challenges for individualised immunosuppression

Calcineurin inhibitors (CNI) represent the most widely used immunosuppressive agents in kidney transplantation. More than 80% of all renal allograft recipients are on CNI therapy
[1]. Since the introduction of ciclosporin A (CsA) in the early 1980s and tacrolimus (Tac) in the 1990s, acute rejection rates have improved remarkably. The current one-year survival rate of a renal allograft exceeds 90%
[2]. In recent decades, the overall renal allograft survival has not improved as expected, indicating a shift of graft failure from early acute rejection to side effects of long-term immunosuppression and chronic rejection. In addition, death with a functioning graft is an important aspect in the long-term follow-up after successful renal transplantation. Cardiovascular (CV) disease is the leading cause of death in kidney transplant recipients (KTRs), with a 3.5% to 5% annual risk of fatal or non-fatal CV events, much higher than in the general population despite adjustment for traditional risk factors
[3, 4].

Undesirable side effects of CNIs, such as nephrotoxicity, metabolic deterioration, aggravation of CV risk factors, as well as the CNI contribution to the development of chronic allograft dysfunction, have come into the focus
[5]. There are many efforts to reduce or withdraw CNIs in order to decrease renal complications as well as other side effects. However, insufficient immunosuppression with an increased risk of rejection should be avoided
[6, 7].

In particular, the development of donor-specific antibodies (DSA) and humoral rejection are the focus of recent renal transplant research
[8]. Concerning the avoidance of relevant side effects, one of the investigational strategies is to minimise CNIs combined with adequate mycophenolic acid (MPA) exposure
[9–11]. This strategy might result in decreased cardiovascular risk, improved renal allograft function and prolonged patient as well as allograft survival.

Adequate monitoring tools are required to optimise the immunosuppressive therapy of an allograft recipient. Particularly in CNIs, as critical dose drugs with a narrow therapeutic range, optimal monitoring strategies are discussed in terms of safety and efficacy
[12]. Nevertheless, no pharmacokinetic (PK) monitoring markers reflect the biological activity of the drug, namely suppression of alloreactive immune responses.

### Pharmacodynamic monitoring as a tool to optimise immunosuppression

Detailed knowledge of the drug-specific mode of action is required to establish and introduce a pharmacodynamic (PD) monitoring assay. The proposed immunosuppressive mode of CsA is the inhibition of the phosphatase activity of calcineurin after binding of the corresponding CNI-immunophilin complexes
[13, 14]. The main substrate of calcineurin in T-cells is the phosphorylated transcription factor ‘nuclear factor of activated T-cells’ (NFAT). NFAT dephosphorylation by calcineurin is required for the nuclear translocation and subsequent transcriptional activation of several key genes of T-cell activation, such as interleukin-2 (IL-2), tumour necrosis factor alpha (TNF-α), and interferon gamma (IFN-γ)
[15].

Recently, a new quantitative analysis of gene expression was employed to measure directly the functional effects of calcineurin inhibition: the transcriptional activities of NFAT-regulated genes in the peripheral blood
[16, 17]. Several evaluations affirmed this approach as a useful tool with the potential to individualise CNI therapy. A high interindividual variability of residual NFAT-regulated gene expression in patients with corresponding CsA or Tac doses has been observed, which confirms various degrees of immunosuppression and T-cell activation. On the other hand, intraindividual variability of residual NFAT-regulated gene expression was low in repetitive measurements in one single patient with a stable CNI dose. This pharmacodynamic monitoring tool might have the potential for precise individual dosing of CNIs
[16, 18, 19].

To date, several evaluations and preliminary studies have been published concerning residual NFAT-regulated gene expression as a specific CNI monitoring tool in clinical practice. NFAT-regulated gene expression in CsA treatment has been evaluated in solid organ recipients, such as kidney, liver and heart in adult and paediatric patient cohorts
[18–27]. All these studies show a cross-sectional or prospective observational design, except for one prospective interventional case-control study
[19]. In this study, 20 stable renal allograft recipients were compared to 20 matched controls to analyse the feasibility of stepwise adaption of CsA dosage by residual NFAT-regulated gene expression. Tapering of CsA resulted in an increase of residual NFAT-regulated gene expression from 6% (1 to 17) to 21% (7 to 32); and resulted in an improved renal allograft function and blood pressure
[19].

Comprehensive data on CsA monitoring by NFAT-regulated gene expression are available, therefore, a prospective randomised interventional trial was established using CsA as a long-term worldwide-used immunosuppression. The Calcineurin Inhibitor-Sparing (CIS) trial is the first randomised controlled study in stable renal allograft recipients to evaluate this immunomonitoring method for tapering of immunosuppression. The rationale and design of the trial are introduced here.

### Research aim and objectives

The CIS trial assesses for the first time in a randomised prospective study, the improvement of the CV risk in stable renal allograft recipients on a CsA regimen by monitoring of standard CsA trough levels (C0s), compared to the novel approach by residual NFAT-regulated gene expression. It takes into account both the need to prevent allograft rejection and to optimise CV risk in an established immunosuppressive regimen.

## Methods/Design

### Study design

The CIS trial (RCHD-1004, protocol version 1.2, 23 December 2013) is a prospective, randomised, parallel-grouped, confirmatory study (Figure 
1). This trial is a single-centre study performed at the Renal Clinic Heidelberg (Department of Nephrology, University Hospital Heidelberg). Stable renal allograft recipients on CsA treatment are randomised, to be monitored and adapted either by CsA C0s or residual expression of NFAT-regulated genes. The study period is six months.

**Figure 1 Fig1:**
[figure not shown]
**Design of the Calcineurin Inhibitor-Sparing (CIS) trial.** CsA, ciclosporin; CNI, calcineurin inhibitor; MPA, mycophenolic acid.

### Selection of the primary endpoint

The primary objective of this trial is to show that a CsA-based immunosuppressive regimen monitored by residual NFAT-regulated gene expression results in a reduced CV risk, compared to monitoring by standard CsA C0s in renal allograft recipients. The CV risk is assessed by the change of arterial stiffness measured by pulse wave velocity (PWV) from baseline to Month 6.

The PWV is an established sensitive marker for the assessment of CV risk, confirmed in a large number of clinical studies including end-stage renal disease (ESRD) population, older or transplanted patients
[28, 29]. In a former study by our group, PWV was significantly lower in renal allograft recipients with a CNI-free regimen in comparison to CsA-treated patients
[30].

### Outcome measures

The change in the arterial stiffness assessed by PWV from baseline (Visit 1) to Month 6 (Visit 3) is the primary efficacy objective of the study. Carotid-femoral PWV pressure as well as central blood pressure will be assessed using a validated SphygmoCor device from AtCor Medical, Sydney, Australia. The assessment of PWV is performed blinded to drug treatment, results of CsA C0 or residual NFAT-regulated gene expression. Measurement of PWV as well as peripheral and central blood pressure is performed at randomisation (Visit 1), Month 3 (Visit 3), and Month 6 (Visit 4).

Secondary efficacy and safety objectives are given in Table 
1. One secondary objective of the CIS trial is to evaluate the two treatment groups with respect to a composite efficacy failure endpoint comprising biopsy-proven acute rejection (BPAR), graft loss or death at the end of the study, consistent with recommendations by the European Medicines Agency (EMEA)
[31]. Additional secondary objectives include individual components of this composite failure endpoint.

**Table 1 Tab1:** **Objectives of the Calcineurin Inhibitor-Sparing (CIS) trial**

Primary objective	To evaluate a CsA-based immunosuppressive regimen monitored by residual NFAT-regulated gene expression concerning reduction in cardiovascular risk assessed by the change in pulse wave velocity from baseline to six-month follow-up, compared to a CsA-based regimen monitored by CsA trough levels in renal allograft recipients
Secondary efficacy objectives	To evaluate, in treatment group:
	- a composite endpoint of biopsy-proven acute rejection (BPAR), graft loss, death and loss to follow-up at Month 6
	- Incidence of BPAR, graft loss, loss to follow-up or death at Month 6
	- S-creatinine and cystatin C at Month 6.
	- Renal allograft function (eGFR calculated by MDRD, Nankivell and Cockroft-Gault formulae) at Month 6
	- Evolution of renal function (S-creatinine) over time by slope analysis
	- Creatinine slope (1/serum creatinine versus time) including the treatment period between baseline and Month 6
Secondary safety objectives	To evaluate, in treatment group:
	- Incidence and severity of adverse events (AEs) and serious adverse events (SAEs)
	- Incidence of AEs leading to discontinuation from the study
	- Incidence of major cardiovascular events (myocardial infarction, apoplexy, peripheral arterial occlusive disease)
	- Pulse wave velocity, aortic pulse pressure, aortic systolic pressure, aortic augmentation index, ejection duration, heart rate variability
	- Changes in blood pressure (central and peripheral pulse pressure, systolic and diastolic, mean arterial blood pressure)
	- Changes in antihypertensive medication (number of antihypertensives)
	- Changes in lipids (cholesterol, LDL-, HDL-cholesterol, triglyceride) and lipid-lowering drugs
	- Changes in glucose levels, HbA1c and antidiabetic therapy
	- Changes in cardiovascular risk (for example Framingham score)
	- Changes in CsA-induced side effects (for example hypertrichosis, gingival overgrowth)
	- Incidence and severity of infections
	- Incidence and severity of malignancies
	- Changes in the quality of life assessed by the ESRD SCL™ questionnaire and SF12 questionnaire
Exploratory objectives	To explore the incidence of DSA in treatment group, and in relation to acute rejection, in a subset of patients at participating centres

BPAR, biopsy-proven acute rejection; CsA, ciclosporin A; DSA, donor-specific antibody; eGFR, estimated glomerular filtration rate; ESRD, end-stage renal disease; HDL, high-density lipoprotein; LDL, low-density lipoprotein; MDRD, Modification of Diet in Renal Disease; SCL, symptom checklist; SF12, Short-Form 12.

For the analysis of laboratory data, venous blood will be drawn prior to medication intake and the blood probe will be analysed in the centre’s local laboratory at each visit. The renal function will be assessed by estimated glomerular filtration (EGF) rate, serum creatinine levels at each study visit, cystatin C at baseline and end of study, and the evolution of renal function (S-creatinine) over time by slope analysis.

Safety objectives include standard assessments of adverse events (AEs) and serious adverse events (SAEs), and specific objectives related to CV events such as hypertension, hyperlipidaemia, and diabetes. In addition, at each study visit, specific objectives that are of concern in renal allograft recipients are assessed, including comorbidities such as malignancies, viral infections and CsA-induced side effects at each study visit. Vital signs will be documented at each study visit and a physical examination carried out at baseline and end of study. In all suspected rejection episodes, an allograft biopsy should be performed prior to or at the latest within 24 hours after the initiation of anti-rejection therapy. Biopsies will be read and interpreted by an independent pathologist blinded to drug treatment according to the updated Banff criteria.

The allograft will be presumed to be lost on the day the patient starts dialysis and is not able to subsequently be removed from dialysis or if the patient undergoes a graft nephrectomy.

Information will be captured at each study visit on CV disease, including angina pectoris that leads to hospitalisation or to intervention, myocardial infarction (segment elevation myocardial infarction (STEMI), non-STEMI), stroke (defined as brain ischaemia due to thrombosis, embolism, or systemic hypoperfusion) and peripheral arterial occlusive disease. At baseline and end of study, the patients’ CV risk will be calculated using the Framingham score
[32].

All patients will be screened for gingival hypertrophy and hypertrichosis at baseline and end of study. Health-related quality of life assessment will be collected by the ESRD symptom checklist (SCL) questionnaire and Short-Form 12 (SF-12) scale
[33, 34] at baseline and end of study. Both questionnaires will be self-completed by the patients.

Exploratory objectives include evaluation of the incidence of DSA in the treatment group. The clinical significance of DSAs - specifically whether or not they contribute to antibody-mediated rejection - is currently a topic under discussion concerning optimising long-term renal allograft function
[35].

Residual NFAT-regulated gene expression will be assessed at every visit in both treatment groups. This will provide additional data on the optimal range of residual NFAT-regulated gene expression in renal allograft recipients, even with respect to allograft function and rejection risk.

A time schedule of enrolment, intervention, assessments and visits is shown in Table 
2.

**Table 2 Tab2:** **Schedule of enrolment, interventions, and assessments**

	STUDY PERIOD			
PHASE	Baseline	Post-allocation		End of study
Visit	1	2	3	4
Day	0			
Month		1 ± 7d	3 ± 14d	6 ± 14d
**ENROLMENT**				
Eligibility screen	x			
Inclusion/exclusion	x			
Randomisation (allocation)	x			
**INTERVENTIONS**				
Intervention A (control group): adaption of CsA according to CsA C0	x	x	x	
Intervention B (investigational group): adaption of CsA according to NFAT-expression	x	x	x	
**ASSESSMENTS**				
Demography	x			
General medical history	x			
Transplantation information	x			
Physical examination	x			x
Vital signs	x	x	x	x
Study medication check		x	x	x
Laboratory test:				
Hematocrit/Biochemistry				
basic program		x	x	
extended program	x			x
Urinanalysis	x			x
CsA C0 and C2 levels	x	x	x	x
NFAT-regulated gene expression	x	x	x	x
Pulse wave velocity	x		x	x
Rejection episodes	as necessary			
Renal biopsy	as necessary			
Adverse events	as necessary			
Severe adverse events	as necessary			
Comments	as necessary			
Concomitant therapy	as necessary			
Immunosuppressive therapy	x	x	x	x
Framingham score	x			x
Quality of life assessment	x			x

C0, CsA trough level; C2, two-hour level; CsA, ciclosporin A; NFAT, nuclear factor of activated T-cell.

### Study population

The study population comprises 55 stable adult renal allograft recipients. The study has broad eligibility criteria and enrols CsA-treated patients with stable renal allograft function. Deceased as well as living donor recipients will be included. The eligibility criteria exclude patients with already significantly deteriorating renal allograft function or a history of chronic active rejection. Specific key inclusion and exclusion criteria are shown in Table 
3.

**Table 3 Tab3:** **Key inclusion and exclusion criteria for the Calcineurin Inhibitor-Sparing (CIS) trial**

Key inclusion criteria	Key exclusion criteria
- Male or female patients ≥18 years old.	- Patients with a history of acute rejection classified > BANFF II, chronic active antibody-mediated rejection or chronic T-cell-mediated rejection.
- Recipients of deceased or living kidney transplants.	- Patients with an EC-MPS dose of <720 mg/d (MMF <1000 mg/d) and MPA-AUC <30 mg^*^h/L.
- Time after the last renal transplantation at least six months.	- Patients with symptoms of significant somatic or mental illness. Inability to cooperate or communicate with the investigator, who are unlikely to comply with the study requirements, or who are unable to give informed consent.
- Stable renal allograft function, defined as S-creatinine ≤3.5 mg/dL and Δ S-creatinine ≤30% during the last three months.	- Females of childbearing potential who are planning to become pregnant, who are pregnant or lactating, and/or who are unwilling to use effective means of contraception, unless
- Patients who are willing and able to participate in the study and from whom written informed consent has been obtained.	a. their career, lifestyle, or sexual orientation precludes intercourse with a male partner, or b. their partners have been sterilised by vasectomy or other means
	- Evidence of drug or alcohol abuse
	- Patients actively taking part in an interventional trial

AUC, area under the curve; EC-MPS, enteric-coated mycophenolate sodium; MMF, mycophenolate mofetil; MPA, mycophenolic acid.

### Patient selection, randomisation and study treatment

All renal allograft recipients of the outpatient clinic of the Department of Nephrology, University Hospital Heidelberg, Germany, will be screened according to inclusion and exclusion criteria. Patients will be enrolled consecutively. After informed consent has been signed, the patient participates in the study. Each patient is uniquely identified by a patient number. The investigator dispenses the patient numbers in chronological order.

Patients are randomised after providing written informed consent in a 1:1 ratio by a web-based randomisation tool using block randomisation with fixed block lengths (Randomisation In Treatment Arms (RITA) randomisation system (University of Lübeck, Germany)). In patients assigned to the standard group (control group), CsA is administered adapted to CsA C0s of 80 to 150 μg/L. In patients assigned to the investigational group (NFAT group), CsA is administered adapted to residual NFAT-regulated gene expression of 15 to 30%. For safety reasons, CsA C0 should be ≥30 μg/L in all patients.

Patients should stay within the target trough blood levels or residual NFAT-regulated gene expression throughout the study. The adaption of CsA dosage starts after randomization as soon as the results of CsA C0 (control group) or NFAT-regulated gene expression (NFAT group) are available, and at subsequent visits, if necessary. Dose adjustments are performed in the control group if CsA whole blood levels are outside the target range of CsA C0 80 to 150 g/L and in the NFAT group if NFAT-regulated gene expression is outside the range of 15 to 30% at the time of study visits (baseline, Month 1, Month 3 and Month 6). Adaption of CsA dose will be performed according to the regular clinical practice in approximately 20% steps. In the case of severe CNI toxicity, dose reductions below the target levels may be performed at the investigators’ discretion. If CsA is interrupted for safety-related considerations for more than four consecutive weeks or more than two episodes longer than two weeks, the patient should be withdrawn from the study.

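### Fixed block lengths at a single centre, where those adapting ciclosporin know the arm, could let some assignments be foreseen; randomly varying, undisclosed lengths would reduce this cheaply

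*Protocol article*

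**What the plan says.** The Protocol article, under Patient selection, randomisation and study treatment, states: "Patients are randomised after providing written informed consent in a 1:1 ratio", by means of a "web-based randomisation tool using block randomisation with fixed block lengths". The block length is not given and no stratification factor is named. The same section says: "The investigator dispenses the patient numbers in chronological order".

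Study design adds: "This trial is a single-centre study performed at the Renal Clinic Heidelberg". One site therefore sees the allocations as they accrue.

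Dosing depends on the arm. The control group is adapted to CsA trough level. For the other arm the text reads: "In patients assigned to the investigational group (NFAT group), CsA is administered adapted to residual NFAT-regulated gene expression of 15 to 30" per cent. Blinding is described in two places, both in Outcome measures: "The assessment of PWV is performed blinded to drug treatment", and an independent pathologist reads biopsies blinded. No blinding of the treating investigators is described.

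Three provisions work the other way, all in the randomisation section. All recipients in the outpatient clinic are to be screened, randomisation follows written consent, and "Patients will be enrolled consecutively".

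**The concern.** In a block of known length, once one arm has used up its places, every remaining assignment in that block is determined. Central web allocation hides the list, but it does not stop someone deducing the next entry from the entries already seen. Here the past entries are visible to whoever adapts the dose, all at one site.

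Foreknowledge matters before consent, when it is decided whom to approach and when. Table 3 leaves some room for discretion: it excludes patients "who are unlikely to comply with the study requirements" and those with significant somatic or mental illness. If a foreseen arm influenced such judgements, the groups could differ in ways that randomisation is meant to prevent. The primary analysis adjusts for age, baseline PWV and eGFR, so a difference in other characteristics would remain. For the secondary event outcomes, Statistical analysis names a log-rank comparison and no covariate adjustment.

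**Working it through.** **Inputs.** 1:1 allocation, fixed blocks, one centre and 55 patients are from the Protocol article. The block length *b* is not given, so lengths 2 to 8 are an assumption, shown as a range. The observer is assumed to know *b* and every earlier allocation, so the results are upper limits.

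**The plan's own figures.** The article gives no figure for predictability. Its sample size reproduces. With an effect of 1.2 and an SD of 1.5, a two-sided unpaired t test at 0.05 has power 0.791 with 25 per group and 0.807 with 26, hence 26 per group. Then 52/0.95 = 54.7, hence 55. Nothing below alters this.

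**Assignments known with certainty, fixed blocks.** In a balanced block of length *b*, the expected number of places left after one arm is full is 2b/(b+2), a share of 2/(b+2). Because 55 is not a multiple of any of these lengths, the last block is cut short:

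| b | Share per full block | Full blocks in 55 | Certain in full blocks | Certain in the cut block | Total of 55 |
|---|---|---|---|---|---|
| 2 | 2/4 = 50% | 27 | 27 × 1 = 27 | 0 | 27 |
| 4 | 2/6 = 33% | 13 | 13 × 4/3 = 17.3 | 0.33 | 17.7 |
| 6 | 2/8 = 25% | 9 | 9 × 1.5 = 13.5 | 0 | 13.5 |
| 8 | 2/10 = 20% | 6 | 6 × 1.6 = 9.6 | 0.6 | 10.2 |

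The entry for the cut block is the expected number per full block less the last place, which is always certain, where only that place is missing: 4/3 − 1 = 0.33 for length 4 and 1.6 − 1 = 0.6 for length 8. For lengths 2 and 6 only the first place of a new block is used, and it is never certain. Simulation of 1,500 sequences of 55 agrees: 27.0, 17.7, 13.5 and 10.1.

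**After the change.** The same simulation was run with block lengths drawn at random, for an observer who knows the set of lengths but not their order. The best guess at each step is the arm more likely to come next.

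| Scheme | Certain, of 55 | Correct guesses overall |
|---|---|---|
| Fixed 4 | 17.7 (32%) | 70.3% |
| Fixed 6 | 13.5 (25%) | 68.0% |
| Mixed 2/4 | 5.9 (11%) | 71.8% |
| Mixed 4/6 | 3.1 (6%) | 68.8% |
| Mixed 4/6/8 | 1.3 (2%) | 67.6% |

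Varying the length removes most of the certainty. It does little to the overall guess rate, because any scheme that keeps the arms close in size rewards guessing the arm that is behind.

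**Cost in balance.** With lengths 4/6 or 4/6/8, the largest possible final difference at 55 patients is 3, that is 29 against 26. The variance factor is 1/29 + 1/26 = 0.07294, against 1/28 + 1/27 = 0.07275 for the closest split, an increase of about 0.3%.

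**The case against.** The case for leaving the text alone has real weight. Screening all clinic patients and enrolling them consecutively leaves little freedom to defer or redirect anyone, and randomisation comes only after consent. PWV is read blinded, the endpoint is a change from baseline, and the model adjusts for three obvious prognostic variables. The article does not say that investigators know the block length; that is a detail a condensed article may leave to the full protocol. Working the length out from the sequence takes some blocks, so early assignments would not be certain, and a very long block would leave few certain assignments. All of this stands, and it limits the point to a risk. It does not remove the risk, because Table 3 includes exclusions that rest on the investigator's judgement.

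A reader might infer that the same clinicians screen, consent, number and dose the patients. The documents do not say so. The randomisation section has the investigator issue patient numbers, Ethical, regulatory and management considerations has an experienced investigator take consent, and Roles and responsibilities has the investigators and the local Study Centre conduct the trial. Who screens and who operates the web tool is not stated. Likewise, the absence of stratification is read from silence in a condensed article.

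Timing is a further objection. Trial status gives October 2013 for the start of recruitment and June 2014 for expected completion. If completion includes the six-month follow-up, the last randomisation would have been due around December 2013, and few or no allocations may remain.

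**Conclusion.** The point holds as an avoidable exposure created by a stated rule. For someone who knows or infers the block length and follows the whole sequence, up to about 27, 18, 13.5 or 10 of the 55 assignments would be certain in advance for lengths 2, 4, 6 or 8. The figures rest on an assumed length, complete knowledge of past allocations and a single unstratified sequence.

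Two stronger readings should be resisted. One is that allocations were in fact foreseen or that the PWV comparison is biased: nothing in the article shows this, and no size of bias in PWV change can be derived from it. The other is that varying the blocks would bring correct guessing down to the 50% of simple randomisation: it stays at about 68% to 72% under the mixed schemes examined. The benefit is confined to assignments known for certain. Alpha, power and sample size are unaffected.

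**What to change.** For all allocations still to be made, set the web tool to randomly varying block lengths, keep the lengths out of any document that investigators see, and amend the sentence in Patient selection, randomisation and study treatment so that it describes randomly varying, undisclosed lengths instead of fixed ones. Moving from fixed 4 to mixed 4/6, for example, would cut the certain assignments from about 18 to about 3 of 55 if applied to the whole sequence, and by proportionately less if applied only to what remains.

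The cost is one configuration setting, one sentence and a possible final imbalance of a few patients, with negligible loss of power. If enrolment has already finished, the present sentence should stay, as a description of what was done, and the trial report should state the block length and whether investigators knew it.
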